### Care-as-usual: hospital-based outpatient cardiology care

Hospital-based outpatient cardiology care is considered care-as-usual. All GPs are allowed to refer non-acute and low-complexity patients with cardiology-related complaints to the hospital-based outpatient cardiology care. These patients receive the same care as within the PC+ centre, i.e. the same diagnostic tests carried out by health-care professionals with the same level of expertise. After the tests the patient meets the cardiologist, the cardiologist explains the results and they discuss further treatment (if needed). This underlines a significant difference with the intervention: in the PC+ centre the cardiologist provides only a recommendation on further treatment and the GP discusses the options for further treatment (instead of the cardiologist), i.e. within PC+ the GP remains in charge. The flow of patients is illustrated in Fig. 1.

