### Sub-study 1: the quantitative study

#### Aim

The aim of the quantitative part is to measure the effects of the PC+ intervention on the population’s health, patients’ experience of care and health-care costs. To measure the effects the researchers will use the following sources: patient questionnaires, data from the cardiology PC+ centre, data from the regional hospital and health insurance claims data. The data will be collected at four different time points, namely at baseline, before the patient has the first consultation with the cardiologist (T0), a week after the first consultation (T1), 3 months after the first consultation (T2) and 6 months after the first consultation (T3). The outcome parameters, including the dimensions, outcomes, concepts, methods and time frame, are summarized in Table 1.

**Table 1 Tab1:** Overview of the outcome measurements

Dimension	Outcome measure	Concept	Method	Data collection time			
				T0	T1	T2	T3
Population’s health	Health status, health-related quality of life	EQ-5D-5 L	Questionnaires	X	X	X	
		EQ-VAS		X	X	X	
		SF-12		X		X	
Experience of care	Effectiveness	EQ-5D-5 L	Questionnaires	X	X	X	
		Number of referrals	Data^a^	X		X	X
	Timeliness	Time between referral of the GP and appointment at the PC+ centre/hospital	Questionnaires	X	X		
	Patient centred	Questions about the experiences of patients with health care	Questionnaires		X		
	Safety	% Hospital admissions	Data^a^				X
		% Emergency care visits					X
	Equity	Subgroup analysis, e.g. educational level and age	Questionnaires	X		X	
Health-care costs	Health-care costs: primary care, PC+, secondary care and diagnostics	Health insurance claims data	Data^a^				X
	Efficiency	Number of consultations	Data^a^				X
		% Hospital admissions					X
		% Patients referred to hospital after PC+					X

T0 – at baseline: before the consultation

T1 – within a week after the consultation

T2 – 3 months after the consultation (follow-up)

T3 – 6 months after the consultation (follow-up)

^a^Data of the PC+ centre, the hospital and Vektis

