### Study population

The study population consists of adult patients (≥18 years) with non-acute and low-complexity cardiology-related health complaints, registered with a GP in the region of the pioneer site. Based on the principles of shared decision-making the GP and the patient will discuss the options for referral which will be either the PC+ centre (intervention group) or the hospital-based outpatient cardiology care (control group). The decision will be based on expertise and experience of the GP, the severity of the complaints of the patient and the preferences of the patient. Less sever, non-acute and low-complex patients should be referred to PC+. At the moment, no specific criteria are included for the referral to PC+. The GP is in charge of referring a patient to the PC+ centre or the hospital-based outpatient cardiology care, i.e. the researchers do not have any influence on the referrals.

Excluded from participation are patients who are already diagnosed with cardiology-related health problems by a cardiologist and patients who have received balloon angioplasty or bypass surgery in the past 18 months. Furthermore, patients with acute health problems who require immediate hospital care and/or patients arriving at the emergency department of the hospital are excluded from participation.

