### Recruitment of patients

Regarding the allocation of patients, this is a practice-based study and therefore the allocation of patients is not random but based on the decision of the GPs. The patient enrolment of both the intervention group and the control group starts when a GP refers a patient to PC+ or hospital-based outpatient cardiology care. Furthermore, it will be statistically tested whether the groups differ in patients’ characteristics at baseline. In case the there is a difference in patients’ characteristics at baseline, the propensity score method (PSM) is used to statistical control for the differences [25]. In addition, the GP will inform all patients about the study. Before the consultation at the PC+ centre or the hospital the patients will receive an information letter with an informed consent form. In this letter they are asked if they would like to participate in the study. All eligible patients have to give informed consent. The flow of participants and the time of measurements, i.e. data collection, are summarized in Fig. 2.

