#### Experience of care

The experience of care will be measured using the perspective of the patient, i.e. the patient’s interaction and experience with the health-care system. The outcome parameters are based upon the six dimensions of health-care performance of the IOM: safety, effectiveness, equity, timeliness, patient-centredness and efficiency [19]. As mentioned above, efficiency will be included in the dimension health-care costs.

Effectiveness of care will be measured with the EQ-5D-5 L questionnaire and the percentage of referrals to hospital-based outpatient cardiology care. On the one hand, effectiveness will be measured using the EQ-5D-5 L scores, where it is analysed whether the health of the population is improved after a follow-up of 3 months. On the other hand, effectiveness will be measured using the number of referrals to hospital-based outpatient cardiology care, where it is analysed whether this number is decreased in the period from 2013 to 2017.

Timeliness of care will be examined by measuring the waiting time (in days) between the day the patient is referred by his GP and the day of the first consultation with the cardiologist.

Patient-centred care will be measured using items based on the Consumer Quality (CQ) index. The CQ index is a standardized method for measuring experiences of patients with health care [38]. The questionnaire (T1) includes 30 questions about the experiences of the patients with health care, with specific regard to their experiences with the health-care professionals (e.g. *‘Did you feel welcome and at ease?’* and *‘Did the health-care professionals listen attentively?’*).

Safety of care will be measured using data that will be made available by the hospital concerning: 1) hospital admissions; 2) emergency care visits.

Equity of care will be examined by performing subgroup analysis on all outcome measures regarding educational level (high versus low) and age (lower than median and higher than median).

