#### Health-care costs

Health-care costs will be measured using health insurance claims data. This study will not cover all related health-care costs but will only focus on health-care costs (including patients’ compulsory deductible). Out-of-pocket payments and indirect costs made from a societal perspective (e.g. labour market, informal care) will not be included. The health-care costs per participant is measured over a period of 6 months after the consultation at the PC+ centre or the hospital-based outpatient cardiology care. This concerns data regarding health-care costs on primary care, PC+, hospital care and diagnostics.

Efficiency of care means, according to the IOM, avoiding waste, particularly waste of equipment, supplies, ideas and energy [19]. With regard to this research, it will be measured whether the number of consultations of patients, hospital admissions and referrals will decrease after the implementation of PC+, which is related to efficient use of equipment and health-care professionals and time of patients. Efficiency of care will be measured using data from the cardiology PC+ centre, the hospital and Vektis. The data will consist of the following items: 1) the average number of consultations at the hospital of a patient over a period of 6 months; 2) the average number of hospital admissions of a patient over a period of 6 months; and 3) the number and percentage of patients that are referred to hospital care after PC+.

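### The patient-level hospital-referral outcome is defined for PC+ patients only, so it cannot show that referrals fall or that PC+ lowers hospital use after screening

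*Protocol article*

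**What the plan says.** In the protocol article, the Health-care costs part of Outcome parameters introduces efficiency by saying that "it will be measured whether the number of consultations of patients, hospital admissions and referrals will decrease after the implementation of PC" (that is, PC+). Three items follow: (1) average hospital consultations per patient over 6 months, (2) average hospital admissions per patient over 6 months, and (3) "the number and percentage of patients that are referred to hospital care after PC". Table 1 repeats item 3 as "Patients referred to hospital after PC", collected at T3 only.

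Study population says that the GP and patient choose "either the PC+ centre (intervention group) or the hospital-based outpatient cardiology care (control group"). Recruitment of patients says that enrolment of both groups "starts when a GP refers a patient to PC+ or hospital-based outpatient cardiology care".

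The care-as-usual section says of the controls: "These patients receive the same care as within the PC+ centre, i.e. the same diagnostic tests". It names the main difference as who discusses further treatment after the tests: the cardiologist in hospital, the GP under PC+.

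The objectives section expects savings partly because many PC+ patients will stay in primary care and use fewer additional hospital services (its third cost mechanism). The analysis section plans a separate two-level linear mixed model for each outcome measure, with a group term (control as reference), time terms and their interaction.

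Separately, the Experience of care section names "the percentage of referrals to hospital-based outpatient cardiology care" as an effectiveness measure. It then specifies the analysis as whether the number of such referrals fell between 2013 and 2017.

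**The concern.** The two groups get the same screening and differ in what follows it. The informative patient-level question is therefore whether fewer PC+ patients than controls go on to hospital cardiology care once screening is done. Item 3 supplies only the PC+ half of that contrast. For controls, a referral to hospital is the entry condition, and the plan forms no counterpart such as the share who remain in hospital care after the first consultation.

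At stake is the claim that PC+ keeps patients out of hospital care who would otherwise have stayed in it. A PC+ percentage well below 100% looks like evidence for that claim. It would look the same if the same share of both groups needed hospital care after screening and PC+ changed nothing downstream.

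**Working it through.** **1. The plan's own figure.** The sample-size section uses p0 = 0.12, p1 = 0.06, p = 0.09, r = 1, z-values 1.96 and 0.84:

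N = (1.96 + 0.84)² × 0.09 × 0.91 × 2 / 0.06² = 7.84 × 0.1638 / 0.0036 = 356.7.

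Unrounded z-values give 357.1, rounded up to the stated 358. This figure concerns the share of cardiology referrals eligible for PC+, not item 3. It is used below only as a group size.

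**2. The definitions side by side.**

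| | PC+ group | Control group |
|---|---|---|
| Entry | GP referral to PC+ | GP referral to hospital outpatient cardiology |
| Index screening counted as hospital care? | No | Yes |
| Item 3 | Share referred to hospital after PC+ | Not defined |
| Item 1 | Hospital consultations, PC+ visit not counted | Hospital consultations, index visit counted |

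**3. Item 3 reported for PC+ alone.** Let q_P be the PC+ share with hospital care after screening and q_C the same share in controls. The effect of interest is q_P − q_C, and the plan defines only q_P. The protocol gives no expected onward-referral rate, so the following values are assumed. With q_P = 50%:

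- q_C = 90% gives −40 points (PC+ lowers hospital use)
- q_C = 50% gives 0 (no effect)
- q_C = 20% gives +30 points (PC+ raises it)

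One reported percentage fits all three.

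**4. Item 3 set against the control group (conditional).** If controls were scored by their entry referral, their value would be 358/358. Fisher's exact test, two-sided:

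- 5 PC+ patients not referred on (353/358, 98.6%): p = 0.062
- 6 not referred on (352/358, 98.3%): p = 0.031

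The probability of at least 6 not referred on, by assumed true onward-referral rate:

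| True rate | Chance of a significant reduction |
|---|---|
| 99% | 15% |
| 98% | 72% |
| 97% | 96% |
| 95% or lower | over 99.9% |

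If both groups share the same post-screening rate q, the true difference is 0, yet the comparison with 100% shows a relative reduction of 1 − q: 10% at q = 0.9, 50% at q = 0.5, 80% at q = 0.2. At q = 0.5 this equals in size the 50% decrease that the sample-size section calls relevant.

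**5. Item 1.** Let both groups have the same mean m of hospital consultations after screening. If the control's screening takes one hospital visit (an assumption), controls average 1 + m and PC+ patients m. The difference is (1 + m) − m = 1 consultation per patient with no downstream effect.

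**6. The 2013 to 2017 count.** This is an aggregate before-after number of hospital referrals. It contains no patient-level value for enrolled controls, so it cannot serve as q_C.

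**The case against.** A reader might infer that the plan tests the PC+ percentage against a control value of 100% and is bound to declare a reduction. The documents do not support this. No section gives controls such a value or names such a test. The planned mixed model could not be fitted to item 3, which has one group and one time point, so its group and time terms cannot be estimated. The only link is the general statement that a model is set up for each outcome measure. Step 4 above is therefore a warning about a possible use, not a description of the plan.

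A reader might also merge item 3 with the effectiveness measure on referrals. That measure is the 2013 to 2017 count, which has its own before-after comparator.

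Three further objections have weight:

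- Substitution is the purpose of PC+. A patient not sent on has avoided a hospital outpatient referral. This stands, and it makes the percentage worth describing. But it follows from where the first visit takes place and says nothing about care after it, which the objectives section claims separately.
- Consultations, admissions, emergency visits and 6-month costs are available for both groups. This also stands, so downstream assessment does not rest on item 3 alone. But item 1 carries the index-visit difference, and admissions and emergency visits do not measure continued outpatient care.
- An article condenses its full protocol. Here, though, the wording of the outcome itself confines it to PC+ patients, so this is more than an omitted detail.

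**Conclusion.** The point holds as one about outcome definition. The patient-level referral item has no control counterpart. Reported alone, it cannot answer whether referrals decrease or whether PC+ reduces hospital use after screening. Item 1 does not fill the gap, because it contains a built-in difference of one consultation per patient if the control's screening takes a single hospital visit. The 2013 to 2017 count is a different outcome and does not supply the comparator.

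The stronger result, that any PC+ rate of about 98.3% or lower would read as a significant reduction at 358 per group, holds only if the item is compared with controls scored by their entry referral. The onward-referral rates used are assumptions. The point affects one part of a central claim of the study and does not invalidate the other comparative outcomes.

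**What to change.** 1. Label the percentage referred to hospital after PC+ as descriptive, for the PC+ group only.
2. Add one outcome defined identically in both groups: any hospital cardiology contact after completion of the index screening, within 6 months of the index consultation. Index screening means all visits needed for the initial tests and the discussion of their results.
3. Take it from the planned hospital and claims data. Count PC+ patients with no hospital contact as zero.
4. Compare the groups with a propensity-adjusted logistic or risk-difference model.
5. Report item 1 also with the index visit excluded.

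The cost is mainly wording and analysis. A rule is needed for when the index screening ends, because the article does not say how many visits the tests take in hospital. The hospital-data section starts its 6 months at referral, so the extract must be checked to reach 6 months after the consultation, the time point that Table 1 uses for T3. The apparent effect will be smaller than a contrast with 100%. Confounding by severity will remain to the extent that the propensity score misses it, since less severe patients are meant to go to PC+.

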### Sample size and power calculation

The sample size and power calculation is based on the referral data of the hospital in 2013 extracted from its registration system. The data of 2013 show that 12% (1755 referrals to hospital-based outpatient cardiology care) of all referrals (14,978 referrals) to the cardiology department of the hospital are eligible for PC+. These eligible patients are referred to hospital-based outpatient cardiology care, which provides, among other health care, the same health care as the PC+ centre. A decrease of 50% in the number of referrals to hospital-based outpatient cardiology care is seen as a relevant difference. So, the number of referrals eligible for PC+ will decrease from 1755 (12% of the total referrals to cardiology) referrals to 878 (6% of the total referrals to cardiology). While assuming a power of 80% and a significance level of 0.05, 358 patients per group (intervention as well as control) are required. Taking into account a dropout of 20%, a sample size of 429 patients per group is required, so this study needs to include 858 patients in total.

To calculate the sample size the following formula was used to compare proportions:$$ N=\frac{{\left({Z}_{\alpha }/2+{Z}_{\beta}\right)}^2\ast p\kern0.2em \left(1-p\right)\left(r+1\right)}{{\left({p}_{0-}\kern0.2em {p}_1\right)}^2\ast r} $$

With the following meaning of the abbreviations:

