**Table Taba:** 

Zα/2 = critical value of the normal distribution at α/2; α = 0.05	1.96
Zβ = critical value of the normal distribution at β; β is 0.2	0.84
p0 = expected proportion of referrals eligible for PC+ at baseline	0.12 (12%)
p1 = expected proportion of referrals eligible for PC+ 1 year after the intervention is implemented	0.06 (6%)
p = (p1+ p0)/2	0.090
r = ratio of patients per group	1

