#### Data analysis

To investigate the effect of PC+ on population health, patients’ experience of care and health-care costs an intention to treat analysis will be conducted. The between-group comparisons will be analysed with multilevel analysis to account for the dependency of observations in time. We will apply a two-level linear mixed model (time, participants) and the level of statistical significance will be set at 0.05 (two-tailed). Separate models (random intercept) will be set up for each outcome measure. The independent variables in each model are a dummy variable indicating the group (control group = reference category), three dummy variables for time (T0 = reference category) and the interaction variable between group and time.

To correct for the possible confounding influence of baseline characteristics of the patients (e.g. age, gender, level of education, native country and health-care costs) and the GP characteristics (e.g. age, gender and practice) a propensity score will be added into the multilevel model. The propensity score will be estimated using a logistic regression model with treatment group (control or intervention) as dependent variables and baseline variables (patient and GP characteristics) included as independent variables. Only baseline variables that are related to the outcome variable (with a *p*-value smaller than 0.10) are included in the propensity score [25].

If normality assumptions are violated, outcome variables will be log-transformed and if necessary non-parametric tests will be used.

SPSS version 22 is used to analyse the data.

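### The 80% power is calculated for a before-after share of all cardiology referrals (12% v 6%) but assigned to 358 PC+ and 358 hospital patients, where no such contrast exists

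*Protocol article*

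**What the plan says.** The section on sample size and power starts from the hospital's 2013 registration data: 1755 referrals, or 12% "of all referrals (14,978 referrals) to the cardiology department of the hospital are eligible for PC"+. It then sets the target effect: "A decrease of 50% in the number of referrals to hospital-based outpatient cardiology care is seen as a relevant difference", that is, from 1755 to 878, or from 12% to 6% of the department's referrals.

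The table of symbols gives the same meaning: "p0 = expected proportion of referrals eligible for PC+ at baseline" (0.12) and "p1 = expected proportion of referrals eligible for PC+ 1 year after the intervention is implemented" (0.06). The contrast is between two periods, and the denominator is all cardiology referrals.

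The result is then attached to different units: "While assuming a power of 80% and a significance level of 0.05, 358 patients per group (intervention as well as control) are required". A 20% dropout allowance raises this to 429 per group and 858 in total.

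Under Study population and Recruitment of patients, these groups are adults with non-acute, low-complexity complaints whom the GP refers either to the PC+ centre or to hospital outpatient care during the study. Under Data analysis, "The between-group comparisons will be analysed with multilevel analysis to account for the dependency of observations in time", with a separate linear mixed model for each outcome, and "the level of statistical significance will be set at 0.05 (two-tailed").

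The section on experience of care plans a look at whether the number of referrals to hospital outpatient cardiology fell between 2013 and 2017.

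**The concern.** The formula returns the number of referrals to sample in each of two periods. The plan uses that number as the count of consenting patients in each of two concurrent groups.

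Within the groups the proportion has no counterpart. Everyone enrolled is a PC+-eligible referral, so the share eligible is 100% in both groups. Referral to hospital outpatient care defines the control group and is at first absent from the PC+ group, so that cannot be 12% v 6% either.

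The enrolment target of 858 rests wholly on this calculation. The article's premises include health that is at least equivalent and safety that is unchanged. Those questions depend on how precisely the enrolled groups can be compared, and the calculation says nothing about that. A reader who takes the 80% as a property of the two groups could credit a non-significant difference in health, admissions or costs with more weight than it has.

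**Working it through.** **1. Reproducing the plan's figure.** Inputs from the table of symbols: z = 1.96 and 0.84, p0 = 0.12, p1 = 0.06, p = 0.09, r = 1.

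N = (1.96 + 0.84)² × 0.09 × 0.91 × 2 / 0.06² = 7.84 × 0.1638 / 0.0036 = 356.7

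This rounds up to 357, and unrounded z values give 357.1. The stated 358 agrees closely, and power at 358 per group for 12% v 6% is 80.2%. The arithmetic is not in dispute.

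**2. What is being counted.**

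| | Sample size calculation | Enrolled groups |
|---|---|---|
| Unit | a referral to cardiology | a consenting patient |
| Denominator | all cardiology referrals (14,978 in 2013) | PC+-eligible patients only |
| Contrast | 2013 v one year after PC+ | PC+ v hospital, concurrent |
| Quantity compared | share eligible for PC+ | health, experience, admissions, costs |

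No row matches.

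**3. The referral question, answered from the register.** The fall regarded as relevant is 1755 to 878.

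- Rate ratio = 878/1755 = 0.500.
- SE(log) = √(1/878 + 1/1755) = 0.0413.
- 95% CI = 0.500 × exp(±1.96 × 0.0413), or about 0.46 to 0.54. This treats the counts as Poisson.
- If each period has about 14,978 referrals (an assumption for the later one), 12% v 6% gives z = 0.06 / √(2 × 0.09 × 0.91 / 14,978) = 18.1. Power is effectively 100%, not 80%, and a relative fall of about 9% would already have power of about 82%.
- Consent and dropout play no part in this comparison.

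**4. What the enrolled groups deliver.** The article gives no effect size, SD or event rate for any PC+ v hospital outcome, so everything below rests on assumptions. The numbers per group are 358, and 343 (429 × 0.8, after 20% dropout).

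*Continuous outcome, one time point.* Detectable standardised difference at 80% power = (1.960 + 0.842) × √(2/n):

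- n = 358: 0.209
- n = 343: 0.214

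For EQ-5D with an assumed SD of 0.15 to 0.25, that is about 0.03 to 0.05. At n = 358, power for other standardised differences is:

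| Standardised difference | Power |
|---|---|
| 0.10 | 27% |
| 0.15 | 52% |
| 0.20 | 76% |
| 0.25 | 92% |

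*Change from T0.* The planned model contains a group-by-time interaction. For a simple change contrast the detectable difference is about 0.21 × √(2(1 − ρ)), where ρ is the correlation between time points. That gives 0.25, 0.21 and 0.16 for assumed ρ of 0.3, 0.5 and 0.7.

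*Admissions, n = 343, two-sided 0.05.*

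| Assumed rates | Power |
|---|---|
| 2% v 4% | 34% |
| 5% v 8% | 36% |
| 5% v 10% | 70% |
| 10% v 20% | 96% |

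None of these figures allows for the precision lost or gained through propensity-score adjustment.

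**The case against.** The strongest reply is that a before-after comparison of referrals is planned. The section on experience of care asks whether hospital referrals fell from 2013 to 2017, and fewer referrals is one of the study's premises. This is true, and the 12%-to-6% effect does correspond to a real study question. But that question is about hospital referral numbers, not 358 enrolled patients per group, and for it the 80% is far too low. Its end point also differs: 2017 in that section, one year after implementation in the table of symbols.

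Table 1 lists the number of referrals at T0, T2 and T3, which suggests that referrals may also be followed in participants. Those times run from each patient's consultation, however, and the row supplies no 12% v 6% contrast between groups. The one referral outcome the article clearly defines on enrolled patients, referral to hospital after PC+, exists only in the PC+ group.

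It is also fair to say that studies are often sized on one outcome, that the article claims no power for EQ-5D, SF-12, admissions or costs, and that how readers would take a null result is a prediction. The difficulty is more basic: the sizing outcome is not one on which the two groups can be compared at all.

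Two further objections stand in part. The detectable differences are illustrations under assumed inputs and simpler than the planned mixed model. And full detail for each outcome may properly sit in the full protocol or analysis plan. Neither removes the mismatch in the article's own text.

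**Conclusion.** The concern holds. The stated 80% power for 358 PC+ and 358 hospital patients belongs to no planned comparison. The number was derived for a share of all cardiology referrals in two periods and then relabelled as patients in two concurrent groups that contain only eligible patients.

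This conclusion rests on the article's own definitions and needs no outside assumption. Its size does depend on assumptions. The register comparison is much more precise than 80% power implies, assuming similar referral volume in both periods. For the group comparison, power ranges from 27% to 92% over standardised differences of 0.10 to 0.25 at one time point, and from about 34% to 96% for a doubling of an admission rate of 2% to 10%. No single corrected sample size can be given, because the article states no target difference for any patient-level outcome.

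**What to change.** Rewrite the sample size paragraph in three steps.

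1. Remove the claim of 80% power for the intervention and control groups.
2. State that the referral question is answered from full register counts, name the periods compared (reconciling 2017 with one year after implementation), and report the rate ratio with its 95% confidence interval.
3. For the enrolled groups, justify the achievable number by the detectable difference or the expected 95% confidence interval width for the main patient-level outcomes (health status, costs, admissions). State the assumed SDs, event rates and correlation, and show a range where they are uncertain.

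The cost is one rewritten paragraph. Enrolment, data collection and the planned models need not change. The price is candour: for uncommon safety events the precision set out will look less favourable than an unqualified 80%.

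### The 20% dropout allowance is added to the required number instead of being divided out, so 429 per group (858 in total) leaves 343 completers, not the required 358

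*Protocol article*

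**What the plan says.** Under the heading on sample size and power calculation, the protocol article bases the study size on a comparison of two proportions: 12% of cardiology referrals at baseline against 6% after PC+ is introduced. It states: "While assuming a power of 80% and a significance level of 0.05, 358 patients per group (intervention as well as control) are required". The next sentence adds the allowance for loss: "Taking into account a dropout of 20%, a sample size of 429 patients per group is required", and concludes "so this study needs to include 858 patients in total".

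The formula is printed, and the table after it lists the inputs. These are 1.96 for the "critical value of the normal distribution at α/2; α = 0.05", 0.84 for β = 0.2, 0.12 for the "expected proportion of referrals eligible for PC+ at baseline", 0.06 for the "expected proportion of referrals eligible for PC+ 1 year after the intervention is implemented", their mean 0.090, and 1 for the ratio r.

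No formula is given for the dropout step. Nothing elsewhere in the article gives the 20% another meaning or corrects the 429.

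**The concern.** A dropout rate applies to the patients enrolled, so the enrolment needed to end with n patients is n / (1 − dropout). Adding 20% of n gives a smaller number, and the final count then falls short of n. The figure of 429 looks like the second calculation.

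What is at stake is the enrolment target, which the article presents as the number that the study needs. If it is wrong, a study that recruits exactly to plan and loses exactly the fraction it expected will still finish below its own requirement and below its stated power.

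**Working it through.** **Inputs** (all from the sample size section and its table): z for α/2 = 1.96; z for β = 0.84; p0 = 0.12; p1 = 0.06; p = 0.09; r = 1; required n = 358 per group; dropout = 20%; stated enrolment = 429 per group, 858 in total.

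**Step 1. Reproduce the 358.** The printed formula is N = (zα/2 + zβ)² × p(1 − p)(r + 1) / [(p0 − p1)² × r].

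- (1.96 + 0.84)² = 7.84
- p(1 − p)(r + 1) = 0.09 × 0.91 × 2 = 0.1638
- (p0 − p1)² × r = 0.06² = 0.0036
- N = 7.84 × 0.1638 / 0.0036 = 356.7

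With unrounded z-values N is 357.1, which rounds up to 358. The figure before dropout is sound.

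**Step 2. Find the source of 429.**

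- 358 × 1.2 = 429.6, which gives 429 if truncated
- 357 × 1.2 = 428.4, which gives 429 if rounded up
- 2 × 429 = 858, the stated total

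Either way the multiplier is 1.2.

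**Step 3. Apply the dropout to those enrolled.**

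- Enrolment needed: 358 / (1 − 0.20) = 447.5, so 448 per group and 896 in total
- Check: 448 × 0.80 = 358.4, which meets the requirement
- Stated target: 429 × 0.80 = 343.2, so 343 per group
- Shortfall in completers: 358 − 343 = 15 per group
- Shortfall in enrolment: 448 − 429 = 19 per group, 896 − 858 = 38 in total
- Dropout that 429 covers: 1 − 358/429 = 0.1655, about 16.5%

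**Step 4. Power by the plan's own formula.** Power = Φ(0.06 / √(2 × 0.09 × 0.91 / n) − 1.96).

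| n per group | Power |
|---|---|
| 358 | 80.1% |
| 343 | 78.4% |

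A standard two-proportion power calculation outside the plan's formula gives 80.2% and 78.5%, so the choice of formula does not matter here.

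**Step 5. Look for another base that would make 429 right at 20% dropout.**

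| Base | n per group | n / 0.80 |
|---|---|---|
| Standard two-proportion formula | 356 | 445.0 |
| Plan's formula, printed z-values, rounded up | 357 | 446.25 |
| Continuity-corrected | 389 | 486.25 |
| One-sided test | 281 | 351.25 |
| Unrounded proportions (1755/14,978 and 878/14,978) | 366 to 367 | 457.5 to 458.75 |

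None gives 429.

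**The case against.** The arithmetic is hard to dispute. The case on the other side is that the error hardly matters.

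- **The loss is small.** It is about 1.7 percentage points of power, and only if the full 20% drops out. The 20% is a round figure with no source given. The rounding of the inputs matters about as much: 1755/14,978 is 11.7%, not 12%, and the unrounded proportions alone raise the base to 366 or 367. This stands as a statement of size. It does not make 429 the answer to the plan's own question.
- **Dropout may not reduce the analysed sample in this simple way.** Referral counts come from PC+ centre, hospital and Vektis records, which an unreturned questionnaire does not affect. The questionnaire outcomes go into a mixed model that uses patients with partial follow-up. This limits the power figure: 78.4% holds for the two-proportion calculation in the sample size section and is not a prediction for every planned analysis. But the plan itself applies a dropout allowance to that calculation, so the allowance has to be worked out correctly there.
- **The route to 429 is inferred.** The article prints no inflation formula, so whether 429.6 was truncated or 428.4 rounded up cannot be told. Neither possibility changes the result, because 429 less 20% is about 343 in both.

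**Conclusion.** The point holds. The required number (358), the dropout rate (20%) and the enrolment (429) stand next to each other, and the third does not follow from the first two. At the assumed dropout the study ends with about 343 per group, 15 short, and by the plan's formula has 78.4% power instead of 80%.

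The conclusion rests on two readings: that 20% means the share of enrolled patients lost, which is the ordinary meaning and the only one the article supports, and that 358 is the number needed after losses, which is how the article introduces it. Starting from 357 instead would still leave the target short, by 14 per group.

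The error would not undermine the study by itself. It should be corrected because a figure that the study relies on is wrong as written and the repair is easy. Whether a change in the share of referrals is a suitable basis for sizing a comparison of two patient groups is a separate question, not judged here.

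**What to change.** Correct the dropout sentence in the sample size section in one of three ways:

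1. State 448 per group and 896 in total, with the formula 358 / (1 − 0.20). This means 38 more patients than now planned.
2. Keep 429 per group and 858 in total, and state that this retains 358 per group for dropout up to about 16.5%.
3. Keep 429 and 858 with the 20% dropout, and state that about 343 per group would remain, giving about 78% power by the plan's two-proportion formula.

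The second and third options cost one reworded sentence and no patients. If the third is chosen, say that the power figure belongs to the two-proportion calculation. In every case print the inflation formula, so that a reader can reproduce the target.
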